# ConFIRM trial - conversion of in vitro fertilization cycles to intrauterine inseminations in patients with a poor ovarian response to stimulation: a protocol for a multicentric, prospective randomized trial

**DOI:** 10.1186/s13063-018-2936-5

**Published:** 2018-10-17

**Keywords:** IVF, Conversion to IUI, Poor ovarian response

## Abstract

**Background:**

To date, there is no consensus on the ideal management strategy of patients with poor ovarian response (POR) to controlled ovarian stimulation (COS) for in vitro fertilization (IVF). Currently, these patients are given the choice of: (1) canceling the cycle; (2) proceeding with COS regardless of the poor response, and performing the oocyte retrieval and transfer of embryos when available; or (3) conversion to an intrauterine insemination (IUI). When the decision to proceed with the COS cycle is taken, it is not clear whether IVF or conversion to IUI is the best choice. If live birth rates were comparable between the two strategies, conversion to IUI would be the better option for poor responders, since it is less invasive and is associated with a lower cost.

**Discussion:**

This is the first randomized controlled trial to compare the outcomes of IVF and embryo transfer to conversion to IUI in patients with POR to COS. If our study shows that conversion to IUI is non-inferior to IVF in terms of clinical efficiency and live birth rate, it would confirm IUI as a better alternative for patients, both individually (less invasive and more patient-friendly) and collectively (lower cost).

**Trials registration:**

ClinicalTrials.gov, ID: NCT03362489. Registered on January 10th, 2018.

**Electronic supplementary material:**

The online version of this article (10.1186/s13063-018-2936-5) contains supplementary material, which is available to authorized users.

## Background

In vitro fertilization (IVF), with or without intracytoplasmic spermatozoid injection (ICSI), followed by embryo transfer, is commonly offered for millions of couples with infertility worldwide. It is usually preceded by controlled ovarian stimulation (COS) with exogenous gonadotropins, which allows to increase the number of follicles and mature oocytes available, thus increasing the number of good-quality embryos available for transfer, and improving the pregnancy and live birth rates (LBRs). However, in about 6% of COS cycles for IVF, less than five mature follicles are obtained despite the use of high doses of exogenous gonadotropins [1, 2]. These cases are referred to as “poor ovarian response to stimulation” (POR), and are associated with lower pregnancy and LBRs. When managing patients with POR during a COS cycle, there are three available options. The first is to proceed with the stimulation despite the poor response, and perform the oocyte retrieval and transfer the available embryos. However, there is a high risk of failure to retrieve oocytes and the absence of embryos to transfer, which should be weighed against the risks of complications associated with the oocyte retrieval and anesthesia. Moreover, such events could be the source of significant disappointment and stress for the couple, and they should be thoroughly counseled before proceeding with the stimulation [3, 4]. The second option is conversion of the IVF cycle to an intrauterine insemination (IUI) in patients having at least one patent tube and adequate semen parameters [5, 6]. Conversion to IUI allows the couple to benefit from the treatments already administered, without the risk of an oocyte retrieval/embryo transfer failure. Finally, the third option is to cancel the IVF cycle. The decision to cancel a cycle is always a challenging one, since it involves not only clinical, but also emotional and financial considerations. Indeed, it is often difficult to announce to a couple the decision to abandon a COS cycle following several weeks of preparation, and after the patient has had several days of high-dose gonadotropin injections. Moreover, several studies have shown that in women with POR, it remains advantageous to proceed with the planned assisted reproductive treatment (ART) [7].

In 2011, the European Society of Human Reproduction and Embryology (ESHRE) published the Bologna criteria in order to “standardize the definition of POR in a simple and reproducible manner” [3, 4]. At least two of the following three criteria are required to establish the definition of POR: (1) advanced maternal age (> 40 years) or any other risk factor for POR; (2) a previous POR (at least three oocytes with a conventional stimulation protocol); (3) an abnormal ovarian reserve test (i.e., antral follicle count (AFC) less than five to seven follicles or anti-Müllerian hormone (AMH) below 0.5–1.1 ng/mL). Moreover, two episodes of POR after maximal stimulation are enough to define a patient as a poor responder according to the Bologna criteria, in the absence of advanced maternal age or abnormal ovarian reserve [3]. However, ever since their publication, these criteria have been the subject of many debates and several revisions have been suggested and requested [5]. Indeed, some aspects have been criticized, such as the supposed homogeneity of the population, the defined thresholds for age, AFC and AMH, the proposed risk factors other than age, and the lack of consideration for oocyte quality compared to quantity [5].

Only five studies compared the outcome of IVF and conversion to IUI in patients with POR [2, 8–11]. These studies have reported that there is no benefit in proceeding with IVF in the presence of only one mature follicle. However, the results in cases with two, three or four mature follicles were divergent. Indeed, three studies reported the superiority of IVF [2, 8, 9], whereas the two others failed to show a difference between IVF and conversion to IUI [10, 11]. Unfortunately, these studies have low levels of evidence, mostly because of their retrospective observational designs, and the presence of multiple biases [2, 8–11]. Therefore, the ideal management of patients with two, three or four mature follicles following COS remains unknown [12]. This is why we have decided to perform the first randomized controlled trial (RCT) to compare these two treatment methods. If our study shows that conversion to IUI is non-inferior to IVF in terms of clinical efficiency and LBR, it would confirm IUI as a better alternative for patients, both individually (less invasive and more patient-friendly) and collectively (lower cost).

### Trial design

This is a prospective, multicenter, parallel-group, open-label randomized controlled and non-inferiority trial conducted at 18 French departments of reproductive medicine (Table 1).

**Table 1 Tab1:** French partners of study

Gynecologists	Center/department
[name]	Coordinating investigator, Angers University Hospital, Angers
[name]	Nantes University Hospital, Nantes
[name] [name]	Caen University Hospital, Caen
[name]	Créteil University Hospital, Créteil
[name]	Rennes University Hospital, Rennes
[name]	Tours University Hospital, Tours
[name]	Strasbourg University Hospital, Strasbourg
[name]	Pointe-à-Pitre University Hospital, Guadeloupe
[name]	Lorient Public Hospital, Lorient
[name]	Clinique Jules Verne, Nantes
[name]	Polyclinique de l’Atlantique, Saint Herblain
[name]	Clinique de la Sagesse, Rennes
[name]	Clinique Pierre Cherrest, Neuilly-sur-Seine
[name]	Polyclinique Jean Vilar, Bruges
[name]	Clinique Léonard de Vinci, Chambray-lès-Tours
[name]	Grenoble University Hospital, Grenoble
Pr [name]	Marseille University Hospital, Marseille
Pr [name]	Antoine Béclère Hospital, Clamart

The study protocol was designed using the recommendations of the Consolidated Standards of Reporting Trial (CONSORT) Statement, Recommendations for Interventional Trials (SPIRIT) 2013 Checklist (Additional file 1) and according to the guidelines of cost-effectiveness studies of the French Health Authority. Eligible patients will be randomized equally to either conversion to IUI or IVF.

### Recruitment

Patients will be recruited in all participating reproductive medicine centers across France. Potentially eligible patients will be pre-identified by the investigator or the co-investigators, based on their medical files and the different selection criteria that can be evaluated at the time, without informing these patients. Patients will be identified during ultrasound monitoring of follicular growth in the course of COS, and those with POR will be handed an information letter explaining the study protocol, so that they are already fully informed by the time they reach ovulation trigger day. The inclusion visit will take place on the day the decision to trigger ovulation is taken. During the inclusion visit, the investigator will thoroughly explain the study and hand the patient an information letter, written in an easily accessible language. The patient who wishes to be enrolled will sign the consent form, and will be randomized to one of the two groups. Randomization will be performed centrally by the trial coordinators using an online randomization module (Ennov Clinical®) in a 1:1 allocation ratio between IVF and conversion to IUI, as shown in Fig. 1. Moreover, randomization will be dynamic, and stratified by: center, number of mature follicles (two, three or four) and age (< 40 or ≥ 40 years).

**Fig. 1 Fig1:**
[figure not shown]
Flow chart. *COS* controlled ovarian stimulation, *V* visit, *IUI* intrauterine insemination, *IVF* in vitro fertilization

### Eligibility criteria

The inclusion criteria are: (1) patients who accepted being included and signed the consent forms; (2) age ≥ 18 and < 43 years and (3) IVF cycle, with and without ICSI, using the “conventional” agonist (long and short) or antagonist protocol, using urinary or recombinant gonadotropins, and having only two, three or four mature follicles (≥ 14 mm) on the ovulation trigger day.

The exclusion criteria are: (1) confirmed bilateral tubal occlusion; (2) non-French speaking patients; (3) partners with severe oligoasthenoteratospermia (OATS) (less than five million motile spermatozoa in the ejaculate); (4) suboptimal stimulation protocols: protocols ≤ 150 IU of daily gonadotropins or mild stimulation protocols or natural and modified natural cycle protocols; (5) couples undergoing IVF for Preimplantation Genetic Diagnosis (PGS) or Preimplantation Genetic Screening (PGS); (6) women under legal guardianship; (7) women with no health or social security coverage and (8) women participating in other interventional trials.

### Study population

At our center, in 2014, we performed 30 IVF cycles following COS with high doses of gonadotropins (≥ 300 IU) in patients at risk of POR. Our clinical pregnancy rate (CPR) was 10% (3/30), and our LBR was 10% (3/30). During that same year, we had 37 IVF cycles which were converted to IUI because of POR. The CPR was 11% (4/37) and LBR was 5% (2/37). If we consider that a maximal difference of 5% between IVF and conversion to IUI is clinically acceptable in order to consider conversion to IUI to be non-inferior to IVF, we will need to include 940 cycles, 470 in each group, to confirm the non-inferiority, with a power of 80%, an α risk of 5% and with 5% of non-evaluable cycles. It is worth noting that patients who are excluded from the study for failure of treatment can be included later on during their next IVF cycle, considering they still fulfill the inclusion criteria.

### Procedures

Patients will be recruited on the day of ovulation trigger. Ovulation will be triggered with an injection of urinary HCG (administered intramuscularly or subcutaneously, 5000 or 10,000 units), or recombinant HCG, depending on the participating center’s protocol.

Patients will be randomized into two parallel arms (Fig. 2): In the “IVF” arm, oocyte retrieval is performed 36 h after the HCG injection, in the operating room, under transvaginal ultrasound guidance, under local or general anesthesia. The procedure lasts about 20 min and the patients are discharged on the same day. The oocytes retrieved from the follicles are transported immediately to the laboratory for fertilization with the partner’s sperm. Fertilization is done either via conventional IVF, or via ICSI, depending on the indication. Embryos are later transferred into the uterus on day 3 or day 5, under ultrasound guidance, in the outpatient department

**Fig. 2 Fig2:**
[figure not shown]
Standard Protocol Items: Recommendations for Interventional Trials (SPIRIT) Figure of ConFIRM study protocolIn the “conversion to IUI” arm (intervention group), IUI is performed 24 to 36 h after ovulation trigger. The partner provides the sperm on site and on the morning of the insemination, and it will be prepared with a two-layer density gradient. Attending physicians, fellows or residents will perform the insemination in the outpatient department, using a soft catheter, with the patient lying in the gynecologic position

### Cost-effectiveness analysis

One of our secondary objective is to perform a cost-effectiveness analysis, in order to determine the optimal treatment strategy for patients with POR to COS, not only in terms of efficiency, but also in terms of cost. We will compare the reference strategy (IVF) to the experimental strategy (conversion to IUI). We will use the incremental cost-effectiveness ratio (ICER), which represents the average incremental cost associated with one additional unit of the measure of effect. IECR is calculated as follows: IECR = *Δ* cost / *Δ* effectiveness. Costs will include the pharmacological compounds, the IVF and IUI procedures, the hospitalization and the potential complications, and will be expressed in euros (€). Moreover, the loss of productivity sustained by the women and their partners during the treatment will also be included in the costs. We will not include the hospital resources used for the COS monitoring (ultrasound scans, blood tests…), nor the ones for the pregnancy follow-up since the treatment method has no impact on the evolution of pregnancy once a clinical pregnancy is confirmed. We will perform a univariate sensitivity analysis (Tornado diagram) to assess the effects of several parameters on the overall outcome.

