### Statistical analysis

We will perform a descriptive analysis of the population’s characteristics. Categorical variables will be expressed as numbers with percentages, and compared using Pearson’s chi-square test or Fisher’s exact test. Continuous variables will be reported as mean values and standard deviations, or medians with 25th and 75th percentile, and compared using Student’s *t* test or Mann-Whitney’s non-parametric test. All statistical tests will be bilateral and a *p* value < 0.05 will be considered statistically significant. We will perform an intention-to-treat and a per-protocol analysis of all outcomes. For the primary outcome, conversion to IUI will be considered non-inferior to IVF if the upper bound of the one-sided 95% confidence interval of the difference in LBRs between the two arms (the rate in IVF minus the rate in conversion to IUI) is ≤ 5%. Analysis of the primary and secondary outcomes will be adjusted according to the stratification variables used for randomization. The primary outcome will be tested using the raw difference in LBRs, and no complex model incorporating the stratification variables will be used. The dynamic randomization on these variables will ensure the variables are well-balanced. Subgroup analysis will be performed according to patients’ age (< 40 vs ≥40 years), the number of mature follicles (two vs three vs four) and patients considered poor ovarian responders according to the Bologna criteria. On the other hand, the cost-effectiveness analysis will be performed on an intention-to-treat basis (the hypothesis being that conversion to IUI is superior to IVF).

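### The planned cost-effectiveness ratio has an expected denominator of zero under the inferred sample-size assumption, and the one uncertainty method named does not show this

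*Protocol article*

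**What the plan says.** The Cost-effectiveness analysis section of the protocol article compares IVF (reference) with conversion to IUI (experimental) and chooses a ratio: "We will use the incremental cost-effectiveness ratio (ICER"), defined as the cost difference divided by the effectiveness difference. The ratio is described as the quantity "which represents the average incremental cost associated with one additional unit of the measure of effect". The section does not say what that unit of effect is. It closes with the only uncertainty method it names: "We will perform a univariate sensitivity analysis (Tornado diagram) to assess the effects of several parameters on the overall outcome".

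The Statistical analysis section puts this analysis on an intention-to-treat basis and adds a direction: "the hypothesis being that conversion to IUI is superior to IVF". The Expected repercussions section says when the result counts: if live birth rates turn out comparable and the economic analysis favours IUI, conversion to IUI is to be called the better option.

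The Study population section gives the pilot figures behind the sample size. For IVF: "Our clinical pregnancy rate (CPR) was 10% (3/30), and our LBR was 10% (3/30"). For conversion to IUI: "The CPR was 11% (4/37) and LBR was 5% (2/37"). It then states a 5-point margin, 80% power, 5% alpha, 5% non-evaluable cycles and 470 per arm, but not the true difference assumed.

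**The concern.** A ratio is a poor summary when its denominator may be close to zero. Here that is the case in which the authors intend to use it: comparable live birth rates mean a small effectiveness difference. The ratio then takes very large values of either sign.

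The sign is also hard to read. If IUI is cheaper, a negative ICER means IUI is cheaper with more births (dominant). A positive ICER means money saved per birth lost. A chance swing of a few births moves the result from one reading to the other.

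A tornado diagram varies one input at a time over a chosen range. It can show which unit cost matters most. It does not show how cost and births vary together across samples of women, which is the uncertainty that matters here. At stake is the economic half of the trial's intended conclusion, which could look firm while resting on a point ratio that another sample would reverse.

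**Working it through.** **Inputs from the protocol article.** Pilot IVF live birth rate 10% (3/30); pilot IUI rate 5% (2/37); margin 5 points; one-sided 95% bound; power 80%; 5% non-evaluable; 470 per arm.

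**Assumptions, not in the article.** Live birth is the effect unit. The mean saving with IUI is €500, €1,000 or €2,000 per woman, with a cost SD of €1,000 per woman. Differences are IUI minus IVF.

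**Step 1: reproduce 470 per arm.**

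n = (z₀.₉₅ + z₀.₈₀)² × [p₁(1−p₁) + p₂(1−p₂)] / (margin − true difference)²

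- With 10% in both arms: (1.645 + 0.842)² × (0.09 + 0.09) / 0.05² ≈ 6.18 × 72 ≈ 446 (rounded up). Then 446/0.95 = 469.5, so 470 per arm and 940 in total. This matches exactly.
- 10% vs 9% gives 665, or 700 after the 5% allowance.
- 10% vs 8% gives 1,184 after the allowance.
- 10% vs 2/37 gives about 55,900 after the allowance.
- 7.5% in both arms at one-sided 2.5% comes near (459). It departs from the stated one-sided 95% bound and in any case also assumes no difference.

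The stated size therefore points to a planned difference of zero.

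**Step 2: spread of the denominator at 10% vs 10%, 470 per arm.**

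SE(ΔLBR) = √(2 × 0.10 × 0.90 / 470) = 0.0196, or 1.96 points. The 95% range is 1.96 × 1.96 = ±3.8 points.

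In 400,000 simulated trials ΔLBR was positive in 48%, negative in 48% and exactly zero in 4.3%. It was within 1 point of zero in about 38%.

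**Step 3: what this does to the ratio.** One birth's difference between arms is 1/470 = 0.213 points. At a €1,000 saving, one birth gives €1,000 × 470 = €470,000 per birth, two give €235,000 and ten give €47,000. The sign depends on which arm has more births.

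Middle 95% of point ICERs in the simulation (trials with ΔLBR = 0 excluded):

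| True LBR, IVF vs IUI | Saving €500 | Saving €1,000 | Saving €2,000 |
|---|---|---|---|
| 10% vs 10% | ±€231,000 | ±€466,000 | ±€936,000 |
| 10% vs 8% | −€141,000 to €204,000 | −€258,000 to €439,000 | −€494,000 to €908,000 |
| 10% vs 5% | €5,500 to €29,600 | €11,600 to €58,500 | €23,600 to €116,900 |

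At 10% vs 8% the births still favour IUI in 13% of trials.

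**Step 4: link to the non-inferiority rule.** With SE 1.96 points, an upper bound of at most 5 points needs an observed IVF-minus-IUI difference of at most 5 − 1.645 × 1.96 = 1.8 points. The two-sided 95% half-width is 3.8 points. So when non-inferiority is declared, the interval for the denominator contains zero, unless IUI is observed to be better by more than about 3.8 points.

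**The case against.** The strongest reply is that this is a condensed article. Naming a tornado does not exclude other analyses, and the Trial design section says the protocol was written "according to the guidelines of cost-effectiveness studies of the French Health Authority". A reader might infer that the tornado is the only uncertainty analysis and that no sampling uncertainty will be shown. The article does not say so: a bootstrap may stand in a fuller plan, and the primary analysis already gives a confidence bound for the live birth difference. What stands is narrower. The one method named does not suit the measure named, and the bound on births is not carried into the ratio.

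Second, a reader might infer that the ICER is bound to be unstable. The zero difference is deduced from the sample size, and at the pilot rates the ratio is fairly steady. This is fair, but those rates put IUI 5 points lower, at the margin itself, so the trial would seldom reach the conclusion for which the economic result is wanted.

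Third, the effect unit is open. If it were a cumulative live birth rate including frozen transfers, the planned zero difference need not carry over. This stands as a limit on the figures.

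Fourth, a reader might infer that superiority will be tested on the ratio. The Statistical analysis section only attaches the hypothesis to the choice of population and names no test. The point is therefore that the hypothesis lacks a workable quantity, not that a wrong test has been specified.

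**Conclusion.** The point holds in limited form. The stated measure works worst in the situation for which the article reserves it, and the uncertainty method named does not reveal this. Under the inferred planning assumption the ratio's sign is close to a coin toss and its size is not reproducible from sample to sample.

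This rests on three assumptions: equal 10% rates (inferred from the sample size), live birth as the effect unit, and the illustrative savings and cost SD. The euro figures scale with the assumed saving; the behaviour of the sign hardly depends on it. With 446 evaluable women per arm instead of 470, the €1,000 range is about ±€443,000, so the conclusion does not change. The primary non-inferiority test is unaffected. This is a worthwhile improvement to a secondary objective that carries part of the trial's intended message.

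**What to change.** 1. Name the unit of effect, and whether it is the primary live birth outcome or a cumulative one.
2. Report incremental cost and incremental live births separately, each with a confidence interval.
3. Resample women within arm, keeping each woman's cost and outcome together (non-parametric bootstrap). Show the cost-effectiveness plane and the acceptability curve.
4. State the superiority hypothesis as incremental net monetary benefit above zero: λ × Δbirths − Δcost > 0, for a stated range of λ, the value per live birth. This involves no division and stays well behaved when Δbirths is near zero.
5. Report the ICER only together with its quadrant.
6. Keep the tornado for unit costs.

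The cost is some extra analysis work and the need to state a range of values per birth, which the article does not give. No new data are needed, provided the planned cost items are recorded per woman. If a fuller plan already contains some of these steps, a sentence saying so would be enough for them.
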